#### Secondary outcomes

##### Readiness to undergo screening

Participants will be asked regarding their level of their readiness to undergo a Pap test within the next month.

##### Cervical cancer screening belief

The cervical cancer screening belief scale consists of 27 items in five scales: perceived susceptibility, seriousness, benefits, barriers, and self-efficacy of cervical cancer screening. Participants will be asked to respond to each item on a 5-point rating scale that ranges from “strongly agree (5)” to “strongly disagree (1)”. A high number selected in their responses would indicate a high level of perceived risk and seriousness of cervical cancer, greater perceived benefits and barriers of screening, and a high level of confidence to undertake screening tests. This scale has been translated into Nepali and Urdu, and tested among South Asian women in Hong Kong with good reliability and validity [28, 29].

##### Sociodemographics questionnaire

Age, ethnic group, monthly household income, years of formal education, marital status, employment status, number of years’ residence in Hong Kong, family history of cancer, and health insurance status of participants will be collected. Data on cues to action to screening (e.g., knowing where to go for screening) and any previous cervical screening experiences will also be collected.

### Data collection

Data for the primary and secondary outcomes (except for the sociodemographics questionnaire) will be collected by a research assistant blinded to arm allocation at three time points: baseline (T0), i.e., upon entry to the study after randomization but before participants receive the intervention; immediate post intervention (T1, 3 months after T0), i.e., upon completion of the intervention; and 3 months post intervention (T2, 6 months after T0), i.e., 3 months after completion of the intervention. The research assistant will contact the participants in both arms to complete the questionnaire. All participants will receive HK$30 upon completing the questionnaire to promote their retention and complete the follow-up.

No data monitoring committee is involved in this study because the intervention is unlikely to introduce a risk or an adverse event to participants.

### Statistical analysis

Data will be double-entered for validation and checked for range before analyses. Data will be summarized and presented using appropriate descriptive statistics. The normality of continuous variables will be assessed using skewness and kurtosis statistics and a normal probability plot. Appropriate transformations, if needed, will be made on skewed variables before entering them into the inferential analysis. The baseline characteristics of the intervention and control arms will be compared by chi-square or independent *t* tests as appropriate. The effectiveness of the CHW intervention will be evaluated by comparing the proportions of subjects in both arms reporting cervical cancer screening uptake at T2 and the changes in level of readiness to take cancer screening at T1 and T2 with respect to T0 between the two arms. The statistical significance of these outcome comparisons will be evaluated using a permutation test, accounting for the potential design effect of the randomization conducted at a cluster level instead of for individual participants [30]. Specifically, differences in uptake rates and changes in the level of readiness will be computed for all possible combinations of arm assignments of the six ethnic minority associations, and the 2.5 and 97.5 percentiles of these differences will be set as the critical values for two-sided permutation tests for the corresponding outcomes. Statistical analyses will also be conducted using SAS release 9.4 (SAS Institute Inc., Cary, NC, USA). All statistical tests will be two-sided with a level of significance set at 0.05.

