### Sample size

The calculation of sample size is based on our previous survey on Hong Kong South Asians indicating that only 37% of them ever had a Pap test [7]. We anticipated that our intervention can increase the rate to at least 60%. By using power analysis software, PASS 14.0 (NCSS, Kaysville, UT, USA), it is estimated that 72 participants per arm will enable a two-parallel arm design with 80% power to detect a rate difference of at least 23% at a two-sided 5% level of significance, assuming the rate in the control is not greater than 37%. To allow for an attrition rate up to 15%, 85 participants in each arm will be needed. Furthermore, to account for potential reduction in statistical efficiency due to randomization by ethnic minority association (cluster) instead of individual participant, a variance inflation factor, called the design effect, is needed to impose on the sample size estimated [25]. The design effect is given by the equation: Design effect = 1 + (*m* – 1) × ICC, where *m* is the average cluster size and ICC is the intracluster correlation coefficient of the underlying outcome. A synthesis study revealed that the ICC tends to be small in primary care research, with a median of 0.005 and an interquartile range of 0.000–0.021 [26]. Allowing for an ICC of 0.021 in our proposed trial, at least 68 participants need to be recruited from each of the six ethnic minority associations—the number of participants in each cluster, *m*, is determined from the equation: number of participants = 2 × 85 × [1 + (*m* – 1) × 0.021] = 6 × *m*.

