### Phase II: implementation of the CHW-led intervention

#### Randomization and blinding

A cluster randomized trial is chosen because South Asian participants who are affiliated with the same center/association likely have close contact with one another through their attendance at the activities held at these centers or associations. Therefore, simple randomization will introduce a high risk of contamination because it can enable participants communicating the knowledge they have gained during the intervention with each other through their close contact, even though they are allocated to different arms.

Six centers and associations, located in districts with a large population of South Asians, have agreed to participate in this study. Each center or association will be randomized to one of the two arms: an intervention arm (*n* = 3) that will undergo immediate treatment (CHW-led multimedia intervention) or a wait-list control arm (*n* = 3) that will receive delayed treatment (the same CHW-led multimedia intervention, but provided after the intervention arm has completed the data collection). Each recruited CHW will be allocated to either arm according to the center or association she is affiliated with.

Research assistant 1 (RA1), who will help to recruit South Asian participants, will not know the subject allocation because recruitment is performed prior to randomization. A statistician, who is independent and blinded to the center/association and collection of data, will generate a random allocation sequence using a computer-generated randomization scheme. Participants from each center/association will be placed in their corresponding arm to avoid “contamination” across participants. Screening uptake and other secondary outcomes will be assessed by another research assistant (RA2) blinded to the arm allocation. CHWs will not be blinded because they are responsible for implementing the intervention. Figure 3 shows the study flow.

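### The permutation test on 3 versus 3 associations cannot give a two-sided p-value below 0.10, so the stated 5% rule either never rejects or runs at about 10%

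*Protocol article*

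**What the plan says.** The section on randomization and blinding fixes the number of clusters: "Six centers and associations, located in districts with a large population of South Asians, have agreed to participate in this study". They are split equally, into "an intervention arm (*n* = 3) that will undergo immediate treatment" and "a wait-list control arm (*n* = 3) that will receive delayed treatment".

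The Statistical analysis section covers uptake at T2 and the changes in readiness at T1 and T2: "The statistical significance of these outcome comparisons will be evaluated using a permutation test". The reference distribution is the set of differences "computed for all possible combinations of arm assignments of the six ethnic minority associations". The rejection limits are then set: "the 2.5 and 97.5 percentiles of these differences will be set as the critical values for two-sided permutation tests for the corresponding outcomes". The section ends: "All statistical tests will be two-sided with a level of significance set at 0.05".

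The Sample size section claims "80% power to detect a rate difference of at least 23% at a two-sided 5% level of significance". It gets there with a two-proportion calculation and a design effect, not with the permutation test. The article gives no other inferential test for either outcome.

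**The concern.** A permutation test can only return p-values that are multiples of one over the number of allocations. With three associations per arm that number is small, and a two-sided test at 0.05 needs a finer grid than this design supplies. The reference set, the cut-offs and the significance level are all written out, and they do not fit together.

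This is the only inference given for the primary outcome, so the trial's main conclusion depends on it. There are two possible consequences. Either no effect, however large, can be declared significant, or a test with a level near 10% is reported as a 5% test. Two details that the article does not fix decide which: how the percentile of 20 values is defined, and whether a result equal to the critical value counts as rejection.

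**Working it through.** **Inputs.** Six associations, three per arm (Randomization and blinding). Permutation over all arm assignments, cut-offs at the 2.5 and 97.5 percentiles, two-sided 0.05 (Statistical analysis). Rates of 37% and 60%, 72 per arm, 15% attrition, ICC 0.021, 68 per association (Sample size).

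**The plan's own figures.**
- The pooled two-proportion formula is n = [1.96·√(2·0.485·0.515) + 0.8416·√(0.37·0.63 + 0.60·0.40)]² / 0.23² = 72.9. That rounds to 73, and power at 72 per arm is 79.5%, so the stated 72 is fair.
- Attrition: 72/0.85 = 84.7, hence 85.
- Cluster size: solving 170·[1 + (m − 1)·0.021] = 6m gives m = 166.43/2.43 = 68.5. From the unrounded 144/0.85 it is 67.9. The stated 68, and 6 × 68 = 408, follow.

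The sample size arithmetic reproduces. It describes a different test from the one planned.

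**Smallest attainable p.** C(6,3) = 20 allocations. Swapping the arms reverses the sign of the difference, also when cluster sizes differ, so the 20 values form 10 pairs of equal size and opposite sign. The most extreme observed result is matched in absolute value by at least its mirror image:

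- smallest two-sided p = 2/20 = 0.10
- smallest one-sided p = 1/20 = 0.05

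Neither depends on the effect, the ICC or the number of women per association.

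**The percentile rule.**
- Empirical percentiles (the SAS default): 20 × 0.025 = 0.5 and 20 × 0.975 = 19.5, which select the 1st and 20th ordered values, that is, the minimum and maximum. The observed difference is one of the 20 values, so it can equal these limits but never exceed them. Rejecting only beyond them has type I error 0 and power 0.
- The same limits, with equality counted as rejection: the extreme pair is rejected, nominal level 2/20 = 10%.
- Linear interpolation: the positions are 1 + 19 × 0.025 = 1.475 and 1 + 19 × 0.975 = 19.525, just inside the extremes. Without ties, the extreme pair is again rejected, nominal level 10%.

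**Simulation.** 40,000 trials per scenario, beta-binomial clusters, ICC 0.021, 58 women analysed per association (68 × 0.85 = 57.8):

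| Rule | Rejection at 37% v 37% | Rejection at 37% v 60% |
|---|---|---|
| Permutation p ≤ 0.05 | 0% | 0% |
| Beyond minimum/maximum | 0% | 0% |
| At or beyond minimum/maximum | 12% | 77% |
| Beyond interpolated percentiles | 8% | 72% |
| t-test on six proportions, 4 df | 5% | 61% |

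The smallest permutation p in any run was 0.10. The spread around 10% comes from ties between equal-sized clusters. With unequal sizes (40 to 98 women; 4,000 runs) both rejecting rules gave 10.4%. At a 5% rate in both arms, where ties are common, the interpolated rule rejected about 6% and the at-or-beyond rule about 16%; the t-test rejected 4.3%.

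**The case against.** The strongest objection concerns which consequence is likelier. A test that can never reject needs two things together: strict exceedance, and a percentile definition that returns the minimum and maximum. The article specifies neither, and although it names SAS it does not tie the permutation test to a SAS percentile definition. Rejecting at or beyond a critical value is a common reading, so a mislabelled test of about 10% is the likelier result. That is fair, but it only chooses between two faults. A significance level that depends on the percentile option or the treatment of equality has not been fixed.

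A second objection is that 10% is approximate. Ties move the realised level both ways, and at very low uptake the interpolated rule happens to fall near 6%. That is an accident of the event rate and cluster sizes. It does not make the rule a designed 5% test, and it never brings the permutation p below 0.10.

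Could the reference set be larger? Counting all 2⁶ assignments would contradict the fixed three per arm. Any restriction would make it smaller: pairing the associations, which the article does not mention, would leave 2³ = 8 allocations and a smallest two-sided p of 2/8 = 0.25.

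The last objection is that the remedy costs power. It does, and this must be stated. With only six clusters, an honest 5% test does not reach the power claimed, which is no ground for keeping a test that cannot reach its stated level.

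**Conclusion.** The point holds. With three associations per arm the smallest two-sided permutation p is exactly 0.10, so no version of the stated rule is a two-sided 5% test by design. It either has zero power or has a nominal level of 10%, realised at about 8% to 12% for 37% uptake and equal clusters. The claimed 80% power at two-sided 5% does not apply to this test. Rejection near that rate (77% at 58 women per association, 79% to 80% at 68) appears only when the level is about 10% or slightly more. The readiness comparisons at T1 and T2 have the same fault.

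The 0.10 bound is exact and assumes only unrestricted 3:3 allocation, as the article describes. The simulated levels and powers also assume beta-binomial clusters, an ICC of 0.021 and, except where noted, equal cluster sizes. Because the faulty rule is stated in full for the primary outcome, it must be corrected before the arms are compared.

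**What to change.** Make the primary test a two-sample t-test on the six association-level uptake proportions, with 4 degrees of freedom. Report the risk difference with its t-based 95% confidence interval. Keep the permutation p-value as supportive, with a statement that it cannot fall below 0.10. Do the same for readiness, using association-level mean changes.

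The alternative is to keep the permutation test as primary and declare its level as two-sided 10%, rejecting when the permutation p-value is at most 0.10 so that the outcome does not depend on a percentile definition. That departs openly from the 5% level in the Sample size and Statistical analysis sections.

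Either change affects only the analysis text, not data or enrolment. Two costs should be stated with it. The t-test assumes roughly normal association-level proportions; its simulated type I error was 5% at a 37% rate and 4.3% at a 5% rate. Its power for 37% v 60% is about 60% with 58 women analysed per association and about 64% with 68, against the 80% claimed, and the Sample size section should say so.

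Adding associations would remove the limit at its source: 4 versus 4 gives C(8,4) = 70 allocations and a smallest two-sided p of 2/70 = 0.029. The trial began on 1 September 2018, so this may no longer be practical.

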### Ethical considerations

Ethical approval has been obtained from the ethical committees of the study institutions. Eligible participants will be briefed on the study details, its aims and objectives, and the rights of the subjects to participate or withdraw at any time. They will be given an assurance in terms of the anonymity and confidentiality before, during, and after the trial. Information collected about the subjects will be kept strictly confidential, and only the research team has access to the encrypted data file. All hard copies of documents will be kept in a locked cabinet and will be destroyed within 6 years of the study’s completion. The electronic data will be kept for 10 years. An information sheet with details of the study and an informed consent form will be provided. Potential subjects interested in the study will be asked to sign the consent form and return it to the CHWs. Voluntary participation will be emphasized among the participants, and they can leave the study at any time without giving a reason. Any protocol modifications will be communicated to the ethics committee and the trial sponsor and registered on the Chinese Clinical Trial Registry.

### Dissemination of results

Results of the trial will be communicated to participants after completion of the study upon request. Findings of the study will be submitted to peer-reviewed academic journals for publication.

## Discussion

To the best of our knowledge, this work is the first cluster randomized wait-list controlled trial to examine the effectiveness of a CHW-led multimedia intervention to increase cervical cancer screening uptake among South Asian women in Hong Kong. This evidence and theory-based intervention addresses the needs of South Asian women with an objective evaluation plan. This intervention is grounded in theoretical models, so findings will also demonstrate how such models can be integrated into the existing mainstream health services to enhance cancer screening uptake.

The combined use of multimedia CHWs in the intervention will potentially provide significant practical implications in addressing related barriers and increasing the uptake of cervical cancer screening among South Asian women. With the use of a multimedia approach in intervention delivery, information related to cervical cancer and cancer screening will be disseminated more effectively to South Asian women who generally have lower educational levels [13]. The navigation assistance provided by CHWs will further help these women overcome difficulties in accessing cervical cancer screening services. In addition, the target population includes hard-to-reach women who are rarely or never screened. Participation in the CHW-led intervention may help them establish their supporting networks and thus contribute positively to their community integration. Results will also be valuable for the government and policy-makers to maximize the community’s capacity to promote health through CHWs.

The strengths of this study include the use of objective measures in examining the uptake of cervical cancer screening by asking the participants to provide receipt of screening utilization. A previous study used a self-report approach to collecting data on cancer screening uptake [31]. However, blinding of participants and CHWs is not feasible in our study because of the nature of the intervention. Nevertheless, primary and secondary outcomes will be assessed by outcome assessors blinded to arm allocation to minimize potential bias of the results.

Certain challenges may be encountered throughout the study. First, the retention of CHWs during the training and implementation of the intervention may be challenging because South Asian women consider that family obligations should be prioritized over other activities, including those for health promotion [32]. In addition, their husbands or mothers-in-law play an influential role in their lives. When the CHWs become occupied by other family issues or their husbands do not allow them to take part in the study, we may need to recruit and train a new CHW to conduct the intervention. Second, the recruitment of South Asian women may be difficult because of the conservative nature of their culture [33]. Their religious beliefs may hamper their participation in this intervention.

To overcome these challenges, we will clearly explain the responsibility of the potential CHWs in this study. The training will be arranged at the time that is most convenient for these CHWs (typically when their children are attending school) and at the community centers located near their homes to facilitate their participation in the training program. We will also allow a longer time frame for the CHWs to complete the delivery of the interventions and thus minimize the disruption in their daily schedules during the study.

Furthermore, we will attempt to build up trust and use a direct approach to recruit potential participants. A South Asian research assistant, who is involved in various health promotion projects, will approach and recruit potential participants when they attend various social and religious activities. When the research assistant establishes a social relationship and rapport with the potential participants, she can easily raise their awareness of the importance of this project, likely facilitating the recruitment process. The familiarity and sensitivity of the research assistant to the cultural norms and religious practices among South Asians can also help alleviate the uncertainties that they may have about this study.

## Summary

South Asian women are significantly at a risk of developing cervical cancer, but their screening uptake rate is low. The proposed CHW-led multimedia intervention will potentially provide significant practical implications in addressing related needs and increasing the uptake of cervical cancer screening of this underprivileged group. The proposed intervention is self-sustainable and can be adopted by different organizations to reduce ethnic disparities on screening if the intervention is proven effective. Ultimately, this intervention may help reduce the healthcare burden posed by cervical cancer by increasing the awareness of South Asian women on the effective prevention of cervical cancer through early detection of the disease.

## Trial status

This trial commenced on 1 September 2018, and the anticipated end date of the study is 31 August 2020.

## Abbreviations

CHW: Community health worker
HBM: Health Belief Model
